### Blinding

Patients and investigators will remain blinded during the trial. The treatment codes will remain blinded until the database is locked for final analysis.

### Pretreatment considerations

Baseline vital signs will be obtained with patients in the sitting and after 3 minutes in the standing position.

Twelve-lead ECGs will be recorded in each patient.

Left ventricular ejection fraction at rest will be determined by echocardiography, using a modified Simpson's rule to calculate LV volumes.

Quality of life questionnaire will be administrated two weeks apart during baseline examination using a translated-validated version of the "Minnesota living with heart failure" questionnaire.

Minimum of two 6-minutes corridor walk test once a week over a 2-week period will be performed. The last value will be used if it is within 10% of the previous value.

### Follow-up period

ECG tracings will be recorded during the security visit and at 1 and 2 years.

Patients will be followed for two years after randomization.

Repeat echocardiograms will be recorded at 1 and 2 years of follow-up along with HF Quality of-life questionnaire and six-minute walk tests.

Clinical measurements will be obtained every three months along with an assessment of treatment adherence and tolerance. Mortality and hospitalization events will be ascertained by telephonic interview and verified with hospital charts review, up to two years after randomization.

### Selection and withdrawal of subjects

#### Inclusion criteria

1. Males or females aged 18 to 70 years.

2. Heart failure symptoms NYHA functional class II to IV

3. Left ventricular ejection fraction <40% determined by bi-dimensional echocardiography using modified Simpson's rule for ventricular volumes.

4. Subjects must be on standard and stable outpatient doses of ACEIs or angiotensin II receptor antagonist for at least four weeks.

5. Subjects receiving diuretics must be on a stable dose for at least two weeks.

6. Clinical Euvolemia: as evidenced by absence of rales, no pleural effusion or ascitis and no more than minimal peripheral edema.

#### Exclusion criteria

1. CHF due to ischemic heart disease, valve disease or any other etiology different than CD.

2. Severe aortic insufficiency

3. Baseline advanced AV block defined as Mobitz type 2 or third degree AV block

4. Serum creatinine >2.5 mg/dl.

5. Resting Heart rate less < 45 bpm

6. Known malignancy and other severe disease which shorten life expectancy < 6 months.

7. Subjects with contraindications for beta-blockers: severe obstructive chronic pulmonary disease, asthma, severe pulmonary hypertension, type 1 diabetes mellitus or history of hypoglicemia.

8. Suspected or confirmed chronic infectious disease including HIV and hepatitis B.

9. History of active substance or alcohol abuse within the last year.

10. Clinically significant psychiatric illness which can negatively affect the subject compliance and participation in the trial.

11. Pregnancy or lactation.

12. Organic disease or gastrointestinal surgery which can affect the oral absorption and pharmacodynamics of the medication under study.

13. Enrollment and participation in other active treatment trial within the previous month.

14. Failure to provide written informed consent.

### Interruption of treatment

Trial treatment should be interrupted under the following conditions.

1. The patient decides it is in his/her best interest.

2. The investigator considers it is advisable or in the patient' s best interest.

3. Intolerable adverse experience(s).

4. Presence of life-threatening conditions despite adjustment of therapy.

If study treatment is interrupted, every effort should be made to reinstate treatment as soon as possible and medically acceptable. The re-initiation dose is determined at investigator' s discretion and the dose may be reduced or re-started at the last dose level. Patients with treatment interruption should continue on the protocol's visit schedule and study procedures except drug dispensing.

### Treatments

The FCV Research Institute (Instituto de Investigaciones FCV) will supply ranurated 5 mg bisoprolol tablets and matched placebo needed for the whole duration of the trial. Study drug and placebo have been kindly provided by Merck Colombia.

### Efficacy assessment

Efficacy assessments will be made at every visit during the trial following randomization. Information will be recorded in the supplied CRF formats dealing with clinical variables, Adverse Events (AE), Serious Adverse Events (SAE) and endpoints.

### Primary outcomes

Primary outcomes are the first occurrence of any of the following:

1. Cardiovascular death.

2. Hospital admission caused by heart failure.

3. Major adverse cardiovascular events: stroke, systemic embolism, resuscitated sudden death.

4. Bradycardia requiring pacemaker implantation.

5. Clinically significant sustained monomorphic ventricular tachycardia causing syncope: sustained ventricular tachycardia or ventricular fibrillation.

Each of the primary endpoints will be recorded on the SAE form and in the individual corresponding form for each endpoint.

### Secondary efficacy outcomes

Secondary outcomes are the occurrence of any of the following:

1. Non-cardiovascular death.

2. Heart failure worsening or mortality related with CHF.

3. New AV block.

4. Need for Implantable cardioverter-defibrillator (ICD), Cardiac resynchronization Therapy (CRT) or Pacemaker therapy (PM).

5. Perceived quality of life worsening.

### Endpoint definitions

1. Cardiovascular death: any death attributable to a cardiac or vascular cause occurring within two years after randomization.

2. Non-cardiovascular death: death from any cause excluding cardiovascular diseases occurring within two years after randomization.

3. Hospital admission/hospitalization caused by heart failure: admission in a hospital or clinic during at least 24 hours caused by heart failure worsening. It excludes procedures and hospitalization for procedures which have been scheduled and not due to worsening of the current heart failure condition since randomization.

4. Heart failure worsening: decline of at least one functional class as defined by the New York Heart Association occurring during any inter- visit period of three months needing inotropic support, IV diuretics, medication dose adjustments or additional drugs for compensation.

5. Perceived quality of life worsening: increase in the "Minnesota living with heart failure" test score of at least 10 points. The test' s score ranges from 0 (best) to 100 (worst).

6. New AV block: appearance of any AV conduction disturbance including first, second and third degree AV block after randomization.

7. Bradycardia requiring pacemaker implantation: ventricular rates < 50 per minute due to any cause including sick-sinus syndrome and AV block, causing symptoms or disability and complying with current indications for permanent pacemaker implantation.

8. ICD: Implantable cardioverter-defibrillator indicated for the prevention and treatment of sudden death, ventricular tachycardia/ventricular fibrillation.

9. CRT: cardiac resynchronization therapy or biventricular pacing or ventricular bifocal pacing for the treatment of advanced heart failure.

10. PM: permanent pacemaker for the treatment of conduction disturbances.

11. Clinically significant ventricular arrhythmias: sustained monomorphic ventricular tachycardia or ventricular fibrillation with symptoms caused by hemodynamic or perfusion alterations, circulatory collapse or syncope.

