### Study development

The study will last 2 years. Patient recruitment will take 12 months with an average follow-up time of 1.5 years per patient.

1. Months 0 to 2: Training of the Personal and techniques standardization

2. Months 2 to 6: Patients recruitment and data recollection

3. Months 6 to 24: Follow up of patients

4. Months 24 to 30: Data analysis

Those subjects with positive serology for *T. cruzy *who meet the inclusion/exclusion criteria will receive placebo or Bisoprolol in addition to standard therapy for chronic heart failure which includes an ACE-inhibitor and may include diuretics or other medication such as digitalis or nitrates for heart failure. Patients included in CHARITY should be on stable doses of an ACE-inhibitor. Diuretics can be added to treatment as needed but patients must be on stable doses of each drug during four weeks prior to randomization.

500 subjects will be randomized in two arms; one will receive oral bisoprolol and the other placebo, during the duration of the study. Forced titration will start with the lowest oral dose of 2.5 mg qd and will be up-titrated in 2.5 mg increments every two weeks until the maximum tolerated dose is achieved or 10 mg qd is reached. In case of intolerance, dose will be reduced to the previously tolerated lower dose. Subjects not tolerating the lower dose of 2.5 qd will have a treatment interruption. The best tolerated dose will be continued for one month, then a security visit will re-asses tolerance. Thereafter patients will be controlled every three months until they complete the mean follow-up period of two years. Standard heart failure therapy with ACE-inhibitors, diurectics, digitalis and nitrates will be strongly reinforced in both parallel arms.

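### Heart failure worsening (secondary outcome 2) cannot be met by a patient while in NYHA class IV, and its three-month interval does not fit the visits up to the security visit

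*Protocol article*

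**What the plan says.** All places are in the protocol article.

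- **Endpoint definitions, item 4.** Heart failure worsening is a "decline of at least one functional class as defined by the New York Heart Association occurring during any inter- visit period of three months", and the decline must be one "needing inotropic support, IV diuretics, medication dose adjustments or additional drugs for compensation".
- **Secondary efficacy outcomes, item 2.** The definition feeds the outcome "Heart failure worsening or mortality related with CHF". It is not a listed component of the primary composite.
- **Inclusion criteria, item 2.** Patients enter with "Heart failure symptoms NYHA functional class II to IV".
- **Study development.** The dose "will be up-titrated in 2.5 mg increments every two weeks until the maximum tolerated dose is achieved or 10 mg qd is reached". Then: "The best tolerated dose will be continued for one month, then a security visit will re-asses tolerance". Three-monthly visits come only after that: "Thereafter patients will be controlled every three months until they complete the mean follow-up period of two years".
- **Efficacy assessment.** Efficacy is to be assessed at each visit after randomisation, with no exception for titration visits.
- **Follow-up length.** The Follow-up period section says "Patients will be followed for two years after randomization", while Study development also gives an average of 1.5 years per patient.

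**The concern.** The definition has two conditions that do not fit the population and the schedule to which it is applied.

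First, the class decline is compulsory. The need for treatment is an added requirement, not an alternative route. A patient already in the worst class therefore has no worsening event while there, however severe the deterioration.

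Second, the decline is tied to an inter-visit period of three months, but the early visits are much closer together. On a literal reading an adjudicator has no qualifying interval until the first three-monthly period after the security visit. The early window is the one in which Study development itself provides for intolerance and dose reduction. If early worsening is more frequent on active drug, leaving it out would make this outcome look better for bisoprolol than it is.

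**Working it through.** The article gives no event rate, power or class distribution for this outcome, so there is no stated figure to reproduce. The check is one of logic and of dates.

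**Class transitions.** With II, III and IV enrolled, the possible declines are II to III, II to IV and III to IV. From IV there is none. A patient who enters in IV can meet item 4 only after improving to III or II and then declining. The share entering in class IV is not given, so the number affected cannot be computed. For scale only, each 5% of the 500 patients is 0.05 × 500 = 25 patients.

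**Visit timeline, all steps completed.**

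- Dose steps: 2.5 mg at week 0, 5 mg at week 2, 7.5 mg at week 4, 10 mg at week 6.
- One month = 365.25 / 12 / 7 = 4.35 weeks. Three months = 3 × 4.35 = 13.04 weeks (unrounded inputs).
- Security visit one month after 10 mg is started: 6 + 4.35 = week 10.35.
- Security visit if a two-week check at 10 mg comes first (an assumption): 8 + 4.35 = week 12.35.
- The longest interval before the security visit is 4.35 weeks, well short of 13.04.

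**Share of follow-up without a qualifying interval on the literal reading.**

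| Follow-up | Weeks | To week 10.35 | To week 12.35 |
|---|---|---|---|
| 2 years | 104.36 | 10.35 / 104.36 = 9.9% | 12.35 / 104.36 = 11.8% |
| 1.5 years | 78.27 | 10.35 / 78.27 = 13.2% | 12.35 / 78.27 = 15.8% |

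A patient whose titration stops at a lower dose may reach the security visit earlier, so the window may be shorter for that patient.

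**Which early events could be lost.**

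| Early event | Where it counts |
|---|---|
| Cardiovascular death | Primary composite |
| Death related to heart failure | Also the mortality half of secondary outcome 2 |
| Heart-failure admission of at least 24 hours | Primary composite (Endpoint definitions, item 3, states no class or interval condition) |
| Worsening managed without such an admission | Among the efficacy outcomes tied to heart failure, only item 4, and there only on a non-literal reading |

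Only the last row is exposed to the interval problem.

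**The case against.** The strongest reply is that this is a wording ambiguity in one half of one secondary outcome, and that three stronger readings are not supported.

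- **Class IV patients can never have the event.** A reader might infer this, but it does not follow. They can improve and later decline, and they remain at risk of the outcome as listed through heart-failure mortality. Nor do non-events that fall equally in both arms distort the risk ratio. They cost absolute risk and precision.
- **The plan excludes titration.** No sentence says so. The three-month phrase can be read as a time window or as a loose label for the usual visit gap, and the Efficacy assessment section points towards counting every visit.
- **All early deterioration on bisoprolol goes uncounted.** It does not. Deaths and heart-failure admissions count from randomisation in the primary composite, adverse events are recorded, and the DSMB reviews safety at least every three months.

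It can also be said that case report forms and adjudicator training may settle how the definition is applied.

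These limits stand, and the point is confined accordingly. What they do not remove is the conflict in the printed text. Assessing efficacy at every visit does not make an event meet a definition tied to a different interval, and adjudicators are to be trained to apply the study definitions uniformly. The ceiling at class IV does not depend on how the interval is read.

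A reader might also carry item 4's restrictions into the primary outcome, because item 3 describes the admission as due to worsening heart failure. Item 3 does not refer to item 4, and the ordinary meaning was probably intended.

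**Conclusion.** The point holds for the worsening component of secondary outcome 2.

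A patient cannot meet that component while in class IV, although class IV is enrolled. This is certain from the text. How many patients it touches is unknown.

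Read literally, the definition also has no qualifying interval before the security visit. That is about the first 10 weeks if every titration step is completed, or about 10% of two years and 13% of 1.5 years. This conflicts with efficacy assessment at every visit. Whether titration was meant to be left out cannot be settled from the article.

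The possible consequence is that worsening in that window, managed without a 24-hour admission, goes uncounted here. That would favour bisoprolol on one condition the documents do not establish: that such worsening is more frequent on active drug. The size of any bias cannot be estimated. The primary composite is not shown to be affected.

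**What to change.** Reconcile Study development, the Inclusion criteria, Efficacy assessment and Endpoint definitions by rewording item 4 in three respects.

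1. **Interval.** Count a decline of at least one NYHA class between any two consecutive visits after randomisation, titration and security visits included, and keep the item's present treatment requirement.
2. **Class IV.** For a patient already in class IV, count documented clinical deterioration of heart failure since the previous visit that needs inotropes or intravenous diuretics. Persistent class IV symptoms alone should not count, since an unchanged patient would then be recorded as worse.
3. **Study drug.** State that a change in study-drug dose alone is not a qualifying dose adjustment. Item 4 does not separate study drug from other medication, and this matters more once titration intervals count.

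The cost is definition wording and matching instructions for the endpoint form and the adjudicators. NYHA class and treatment changes must be recorded at the titration visits, which already exist. No dose, schedule or treatment rule changes. The downsides are that some more early events will be counted, and that the class IV criterion differs slightly from that for the other classes.

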### Monitoring committees

#### Steering committee

The Steering Committee is composed of a group of national leaders who will mostly be cardiologists, since patients with CHF and Chagas' disease are most often cared for by cardiologists. This group will be supplemented with experts in neurology, electrophysiology, coagulation and thrombosis.

The committee has the overall responsibility for producing and conducting a scientifically sound design and ensuring accurate reporting of the study. In that capacity, the Steering Committee must address and resolve scientific issues encountered during the study. This committee will meet at least twice a year. The main role of the Steering Committee is the development of the protocol and CRF and to ensure appropriate conduction of the trial. The steering committee is composed by the principal investigators and site investigators. The chairman of the steering committee is the principal investigator. All proposed ancillary research investigations on patients enrolled in CHARITY must be approved by the Steering Committee. The primary scientific publication reporting the study results is the responsibility of the Steering Committee. Collaborating Investigators or members of the various study committees wishing to prepare secondary publications must submit proposals and manuscripts to the Steering Committee for approval. The final decision on the contents of all publications will be the responsibility of the CHARITY Operations Committee.

#### CHARITY Operations Committee

The Operations Committee will consist of a select group of Steering Committee members chosen for their specific expertise and experience. This group will be responsible for ensuring that study execution and management are of the highest quality. The Operations Committee will convene regularly by teleconference and/or face-to-face meeting (at least every 2 months) to discuss and report on the ongoing supervision of the study. Issues relating to regulatory reporting are the responsibility of the Sponsor, although the Operations Committee is to be kept informed of these activities. The Operations Committee will determine its own guidelines and approve the criteria and guidelines of the other committees prior to commencement of the study. The Operations Committee will need to determine its own working guidelines, especially regarding the decision-making process on specific aspects of the study conduct. Throughout the trial, the Operations Committee will monitor the overall number of confirmed primary events and may decide to increase the sample size in order to maintain or enhance the statistical power of the study.

### FCVRI project office

The FCVRI Project Office is located at the Instituto de Investigaciones/FCV in Bucaramanga, Santander, Colombia. The FCVRI Project Office is independent and its primary function is to facilitate and oversee the execution of the study. The FCV Project Office will keep the Operations Committee appraised of the progress and conduct of the trial and will provide ongoing administrative and methodological support to the Event Adjudication Committee and the DSMB. It will also make available appropriate study data and/or documentation to these committees.

Oversight activities of the FCCVProject Office include the following :

1. Develop and manage the Central Study Database, perform data entry and validate records in the DataFax system:

2. Implement and manage the central randomization system;

3. Generate patient visit schedules for all centres;

4. Compile and generate monthly study status reports for general distribution to all personnel involved in the study, centrally and locally;

5. Maintain necessary communication with all National Investigators and study personnel in order to provide methodological and administrative assistance to them, so that the requirements of a well-disciplined and successful trial can be fulfilled;

6. Provide appropriate reports every two weeks in order to facilitate and optimize site monitoring and study drug distribution;

7. Perform the final analysis for scientific publication.

The FCVRI Project Office will also collaborate in the following areas:

1. Ensure protocol adherence;

2. Assess timely completion and submission of Case Report Forms (CRFs) and support documents;

3. Monitor quality and homogeneity of all data processing activities;

4. implement appropriate measures for data quality control.

As part of the overall study management, the FCVRI Project Office will prepare and distribute monthly status reports to all collaborators at the central and local level, including investigators. The primary purpose of these reports will be to keep all Investigators informed of the performance at their Clinical Centre in relation to the combined performance of the other participating Clinical Centres. These reports will contain the following information:

1. Patient accrual rates

2. Permanent study drug discontinuations

3. Overdue clinical assessments

4. Projected patient follow-up schedules

### Data and Safety Monitoring Board (DSMB)

CHARITY will be conducted in a double-blind manner in which patients and treating physicians are blinded. The trial management team (Operations Committee, Event Adjudication Committee, and the FCVRI Project Office) will also be blinded with respect to treatment allocation. The DSMB will include at least 2 prominent cardiologists and a neurologist, as well as a statistician. Their mandate will be to provide on-going review of the safety of all the investigational treatments. To facilitate its responsibilities, the DSMB will have an Associated Statistician who will receive study data directly from the Central Study Database and who will remain independent of the trial management team. The DSMB Associated Statistician is not a member of the DSMB, but presents data to the committee and is responsible to the Chairman. The DSMB Associated Statistician, being unblinded, will not be able to edit/alter any part of the Central Study Database. Routine access to the treatment code will be restricted to the Chairman of the DSMB, except for emergency unblinding on a case by case basis.

